# Ferritin screening and Iron treatment for maternal anemia and fetal growth restriction prevention - A multicenter randomized controlled trial (FAIR Study)

**DOI:** 10.12669/pjms.39.1.6686

**Published:** 2023

**Keywords:** Non anemic iron deficiency, Maternal anemia, Fetal weight restriction

## Abstract

**Background::**

Non-anemic iron deficiency precedes iron deficiency anaemia and has an estimated prevalence of 1-2 billion worldwide. Few studies have comprehensively researched the idea of treating non-anemic iron deficiency (NAID) with iron to improve the outcome of the mother and the offspring.

**Methods and Analysis::**

FAIR will be a multicenter randomized controlled trial that will be conducted in multiple clinical academic obstetrics units in Lahore (including Services Institute of Medical Sciences, Lahore, Allama Iqbal Medical College, Lahore and Fatima Jinnah Medical University). Pregnant women at gestational age <20 weeks with hemoglobin 11-13 g/L and ferritin below the threshold (<30 ng/ml) will be invited to take part in the study. Randomization will be done by computer based generated random numbers. One group (usual care or oral group) will be offered routine care prophylactic dose of oral iron (30-45 mg/day) and the other group (intervention arm or IV group) will be offered therapeutic dose of IV iron (dose calculated by Ganzoni formula) in addition to usual care. All patients will be followed up till delivery. Primary maternal outcome will be hemoglobin at 36 weeks’ gestation. Secondary outcomes are fetal birthweight or small for gestational age, preterm birth, preeclampsia, multidimensional fatigue inventory, breast feeding initiation, blood transfusion, and fetal cord ferritin and hemoglobin.

**Discussion::**

The study will generate evidence as to whether screening serum ferritin in non-anemic pregnant women and replenishing their iron stores will likely reduce the rate of predelivery anemia in pregnant women, improve birthweight and preventing perinatal complications.

**Steering committee::**

has an independent chair [name], one expert member [name] and [name] to represent patients, public and consumers. Trial steering committee with independent chair and member with a patient representative will oversee the study. Chair of steering committee has the authority to stop the trial whenever needed in case of positive or negative results. Steering committee meetings will be held on annual basis.

**Independent Data monitoring committee::**

comprises of [name] as chair and [name] and [name] [name] as members. Data monitoring committee will assess the progress, data safety and if needed critical efficacy points of the clinical study and will show their results quarterly in data interim meetings. The committee will focus on integrity of the whole process and compliance of all sites with all aspects of the protocol. It will perform confidential interim analyses quarterly, which may be used to determine if an effect is observed and if the study should continue to its planned sample size. Data monitoring committee will report to the Chair of the steering committee.

**Trial Registration No:** NCT04228627 www.clinicaltrials.gov (Dated 14 January 2020)

**Version Date/ No:** Version 1.3 Updated 06.05.2021

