### Sample Size:

Using haemoglobin at 36 weeks as a continuous outcome measure and to confirm or refute a small to medium effect of screening/intervention vs usual care (0.3 SD difference), based on ? = 0.05 and β = 0.1 (90% power), 235 patients in each group (i.e. 470 patients in total) will be required. Considering a 20% loss to follow-up, the sample size is inflated to 300 patients in each group (i.e. 600 patients in total).

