### Data Analysis:

All the statistical analysis will be done on statistical package for social sciences (SPSS). Mean and standard deviation will be calculated for continuous variables like age, gestational age, haemoglobin, serum ferritin levels etc. Frequency and percentages will be calculated for categorical variables like gender. If data are not normally distributed then median will be used. Confounders like age, duration of disease and co morbidities will be controlled through multivariable analysis documented through a statistical analysis plan prepared before the outcome data per group are unblinded. Comparison of outcome will be tested by chi-square and student’s t-test. P value of <0.05 will be significant.

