### Data Monitoring:

Trial steering committee with an independent chair and membership including a patient representative will oversee the study. Data monitoring committee will perform confidential interim analyses, which may be used to determine if an effect is observed and if the study should continue to its planned sample size. Any adverse reaction to IV Iron or blood transfusion will be noted and entered in specific transfusion reaction registers in wards according to hospital protocol. Independent data monitoring committee will systematically review all trial related activities, data entry, will assess compliance with regulatory requirements for clinical trial protocol and clinical quality management plan by principal investigator and all sites support personnels and audit trial quarterly to identify potential risks and help to ensure that compliance issues do not jeopardize the trial.

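### Quarterly looks for an effect and an open-ended power to stop sit beside a single P<0.05 and a one-look sample size, so the plan as written does not hold its 5% type I error

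*Protocol article*

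**What the plan says.** Five places in the protocol article bear on this.

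- **Independent Data monitoring committee.** The committee looks at efficacy if needed and reports to the steering committee chair. On its interim work: "It will perform confidential interim analyses quarterly, which may be used to determine if an effect is observed and if the study should continue" to the planned sample size.
- **Data Monitoring.** The same purpose is repeated without the frequency: "which may be used to determine if an effect is observed and if the study should continue to its planned sample size".
- **Steering committee.** "Chair of steering committee has the authority to stop the trial whenever needed in case of positive or negative results". The committee itself meets once a year.
- **Data Analysis.** Outcomes are compared by chi-square and t-test, and "P value of <0.05 will be significant". No other threshold appears. A separate statistical analysis plan is mentioned in connection with multivariable control of confounders.
- **Sample Size.** The primary outcome is continuous haemoglobin at 36 weeks, the target is a 0.3 SD difference, and the error rates and size read "0.05 and β = 0.1 (90% power), 235 patients in each group". This is then raised to 300 per group for 20% loss to follow-up.

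**The concern.** A threshold of 0.05 gives a 5% false-positive rate when the data are tested once. If the data are tested repeatedly and the trial may stop at the first significant result, each further look adds a chance of a false positive. The article commits to looks whose stated purpose is to detect an effect, attaches a decision to continue or stop, and leaves that decision unbounded. The one threshold it gives and the sample size it derives both belong to a single final test.

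Two things are at stake. First, the error rate of the primary claim is undefined, so a positive early stop would be open to challenge. Second, a trial that stops early on P<0.05 tends to exaggerate the effect, because only a large observed difference can cross that line with few patients.

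**Working it through.** **1. Reproduce the stated sample size.** Inputs from Sample Size: difference 0.3 SD, alpha 0.05, power 90%. Sidedness is not stated.

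n per group = 2 × (1.960 + 1.282)² / 0.3² = 2 × 10.507 / 0.09 = 233.5, so 234. The t-test version gives 234.5, so 235, as stated. A one-sided test gives 191, which does not fit. The design is therefore a two-sided, single-look calculation. Allowing for 20% loss gives 235 / 0.8 = 294, which the plan rounds to 300; 80% of 300 is 240 evaluable per group. The size is not in dispute, and no term for repeated looks enters it.

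**2. Type I error under repeated looks.** Assumptions, none stated in the article: K equally spaced looks including the final one, two-sided |Z| > 1.96 at each, stop at the first crossing. The overall error is

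1 − P(|Z₁| < 1.96, …, |Z_K| < 1.96), with corr(Z_i, Z_j) = √(i/j) for i < j,

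evaluated by recursive numerical integration. For K = 2 the correlation is √(1/2) = 0.707 and the result is 8.3%.

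| Looks (K) | Overall error | Multiple of 5% |
|---|---|---|
| 1 | 5.0% | 1.0 |
| 2 | 8.3% | 1.7 |
| 4 | 12.6% | 2.5 |
| 6 | 15.5% | 3.1 |
| 8 | 17.6% | 3.5 |
| 12 | 20.7% | 4.1 |

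One interim look plus the final one is enough to exceed 5%.

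**3. How many looks are informative?** Enrolment is before 20 weeks and the outcome is at 36, so each woman needs more than 36 − 20 = 16 weeks to reach it. A quarter is about 13 weeks. A look one quarter after the first enrolment can therefore hold almost no primary outcome data. K in the table counts informative looks, and these are fewer than the quarters elapsed.

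**4. Size of effect needed to cross early.** With 235 per group at full information, the smallest observed difference giving P<0.05 is 1.96 × √(2/n) SD.

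- At one quarter of the data (n about 59): 1.96 × √(2/59) = 0.36 SD.
- At one eighth (n about 29.4): 1.96 × √(2/29.4) = 0.51 SD.

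Both exceed the design effect of 0.3 SD.

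**5. What a boundary would do.** The same recursion gives, for K = 4, 8 and 12:

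- Interim P<0.001 with final P<0.05: overall error 5.1%, 5.2% and 5.3%.
- O'Brien-Fleming, overall error held at 5%: final-look P 0.043, 0.038 and 0.036.

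Power can be checked at 240 evaluable per group, where the expected final Z is 0.3 × √(240/2) = 3.286. Counting only crossings at the final look, the first rule gives Φ(3.286 − 1.960) = 90.8%. The four-look O'Brien-Fleming rule gives Φ(3.286 − 2.024) = 89.7% on the same count, and earlier crossings add a little to that.

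**The case against.** The strongest reply is that this is a condensed article. Boundaries, number of looks and alpha spending commonly sit in an analysis plan or a monitoring charter, and neither is shown. That stands as a caution: a sound interim rule may exist. It does not dispose of the point, which rests on what the article fixes rather than on what it leaves out. The article positively sets a frequency, an efficacy purpose, one threshold and a power to stop whenever the chair sees need. A boundary elsewhere would still conflict with that open-ended power, and the article cites its analysis plan only for confounder adjustment.

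The second reply is that P<0.05 is never named as the interim threshold. It appears under Data Analysis for the outcome comparison, and efficacy is reviewed only if needed. This also stands, and it is why the inflation can only be stated conditionally. With interim P<0.001 there would be almost none.

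Third, the steering committee meets annually, which might suggest fewer decision points. The chair's authority is not tied to those meetings, so this does not settle the number.

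A reader might also infer three stronger things that the documents do not support:

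- **That the false-positive rate is three to four times the nominal 5%.** That needs about 6 to 11 informative looks, all at 0.05, and no such number is given.
- **That stopping for negative results raises the false-positive rate.** It does not. Stopping for lack of effect can cost power, by an amount that cannot be derived here.
- **That confidential analyses contradict results being shown at interim meetings.** The audience of those meetings is not stated, and closed meetings would fit the wording.

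**Conclusion.** The point holds in conditional form. The article combines quarterly looks for an effect, an unbounded authority to stop, one threshold of P<0.05 and a single-look sample size. Followed as written, these do not secure a 5% type I error.

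The size depends on the number of informative looks and on the P value used at each. If every look is tested at 0.05 and looks are equally spaced, the overall error is about 8% for 2 looks, 13% for 4, 18% for 8 and 21% for 12. No single multiple can be asserted, because the article gives neither the number of looks nor the duration, and an unseen document may hold a stricter interim rule. The sample size itself reproduces.

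**What to change.** Make the following changes to the wording.

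- **Independent Data monitoring committee and Data Monitoring:** say that the quarterly meetings review safety, recruitment and compliance. State how many efficacy looks there will be, and define each by the number of women with a 36-week haemoglobin rather than by calendar quarter.
- **Boundary:** name one that controls alpha, or point to the document that holds it. O'Brien-Fleming-type Lan-DeMets spending is one choice. Interim P<0.001 with final P<0.05 is another, with overall error about 5.1 to 5.3% for 4 to 12 looks. A single efficacy look is simple, but several looks under a spending rule are equally valid.
- **Steering committee:** replace the open authority to stop for positive or negative results with a reference to that boundary. Make any futility guideline explicit and non-binding.
- **Data Analysis:** state that P<0.05 is the overall two-sided level, and give the final-look threshold that follows from the boundary.

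The cost is that an early efficacy stop becomes harder to reach and the final threshold may fall slightly below 0.05. No more patients are needed: the planned 300 per group already yields 240 evaluable after 20% loss, against 235 required, and this keeps power close to 90% or above under the boundaries checked.

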## INTRODUCTION

Anemia is the world’s second leading cause of disability with a global prevalence of 38% amongst pregnant women.^1^ It affects more than 56 million women worldwide, two-thirds being from Asia.^2^ Iron deficiency accounts for majority of the cases and is the most common cause of anemia worldwide. Iron requirements increase 10-fold during pregnancy from 6 mg/day to 22 mg/day. Diet alone cannot meet this huge demand, so first the iron stores are used up and then iron deficiency aneemia sets in. Studies from developed countries also report prevalence of iron deficiency among 24-40% of women.^3^,^4^ This situation is escalated in low-middle income countries (LMIC) where women enter pregnancy with low stores, hence they develop iron deficiency anemia early and more severely. The prevalence of anemia in pregnant women in LMIC is estimated to be 45-50%.^5^-^7^ Multiple factors including iron deficient diet, short inter pregnancy interval and parasitic infections are responsible.

Iron deficiency anemia is detrimental to pregnant mothers both in terms of physical and mental wellbeing. It is associated with antepartum, intrapartum and postpartum morbidity in terms of increased fatigue, vertigo, leg cramps, irritability, postpartum hemorrhage, increased chances of sepsis and postpartum depression.^8^,^9^ The fetus is entirely dependent on maternal iron stores or daily maternal iron absorption for its supply of micronutrients. Offspring compromise in terms of low birth weight, prematurity, growth restriction, increased perinatal mortality and neonatal anemia subsequent to birth is reported.^10^,^11^ Children born to anemic mothers are reported to have low IQ at seven years of age.^12^ Birth weight is an important determinant of child survival, and low birth weight children are at increased risk of ill health and mortality.

WHO defines anemia in pregnancy as hemoglobin < 11gm/dl in any trimester.^13^ UK antenatal guidelines define hemoglobin less than 11 gm/dl in first trimester and <10.5 gm/dl in second and third trimester as anemia in pregnancy.^14^ Iron deficiency is tested by a laboratory test of ferritin and complete blood count (CBC) including hemoglobin concentration and red blood cell indices. International Federation of Gynecology and Obstetrics (FIGO) recommends a minimum prophylactic dose of 30 mg/day iron supplementation in pregnancy in areas of high prevalence of anemia and 100-200mg /day is recommended as treatment in mothers with established iron deficiency anemia.^15^ Pregnancies with iron deficiency anemia are treated according to established protocols with oral and parenteral iron.^15^-^18^ Oral iron is substituted with parenteral iron in women who do not tolerate oral preparations well. Daily prenatal use of iron supplementation has been reported to result in improved birth weight in a linear dose response fashion.^19^ World Health Assembly has set a target of 50% reduction of anemia by 2025. A reference document has been designed by WHO for policy makers to implement programs of detection and control of anemia at regional and national levels.^20^

There is a spectrum of iron deficiency in pregnancy ranging from iron deficiency without anemia to iron deficiency anemia. Non-anemic iron deficiency (NAID) precedes iron deficiency anaemia and has estimated prevalence of 1-2 billion worldwide.^21^ All pregnant women at their booking visit are offered CBC but routine testing of serum ferritin is not common in clinical practice. Serum Ferritin is the most sensitive test of iron deficiency and low levels reflect a state of depleted iron stores.^22^ Different thresholds of serum Ferritin are described for diagnosis of iron deficiency anemia in various studies.^23^ Recent UK guidelines on management of anemia in pregnancy recommend that non anemic women at risk of iron deficiency should be identified and have their serum ferritin checked. Serum Ferritin < 30L is indicative of iron deficiency.^24^ The test for iron deficiency with serum ferritin level <30 /L has sensitivity of 92% and specificity of 98%. Few studies have comprehensively researched the idea of treating NAID with iron to improve the outcome of mother and offspring. Studies on NAID suggests a variety of possible benefits of iron supplementation on infant birth, educational attainment, infant development and maternal fatigue.^25^ There is lack of robust evidence that treatment of NAID will result in significant benefit to mother and fetus in terms of prevention of low birth weight. The clinical consequences of NAID in pregnancy are largely unknown and there is a need to determine through research if there is a need for a national screening program for early detection and intervention.^26^ There is multidisciplinary willingness to put this hypothesis to test in a robust trial.^27^ All woman who book themselves at antenatal hospitals if screened with a serum ferritin test can be offered therapeutic doses of iron, which can lead to prevention of maternal and fetal complications of iron deficiency.

The rationale of this study is to observe the outcome of NAID in pregnant woman in terms of hemoglobin at 36 weeks’ gestation in addition to secondary outcomes including birth weight, preterm birth, development of preeclampsia in the mother, multidimensional fatigue inventory (MFI), breast feeding initiation, blood transfusion, fetal cord blood ferritin and hemoglobin. It is aimed at the hypothesis that early screening and treatment of iron-depleted non-anemic women will reduce the risk of developing maternal anemia and prevent complications like low birth weight or small according to their gestational age in babies. This is the first trial of its kind in Pakistan.

### Hypothesis:

The NAID women who are given therapeutic doses of IV iron will more often have normal maternal haemoglobin at term and normal birth weight of the baby as compared to the NAID women who are given usual care.

### Trial design:

It is a parallel, two-arm (intervention-control) and double blind (care providers and outcome assessors both blind) randomised controlled trial of IV Iron intervention provided to NAID women to replenish their iron stores compared with usual care with prophylactic oral iron. Eligible participants are randomized to the intervention and usual care groups. A 600 sample size will be recruited from three centers. All patients will be followed up till delivery. Post randomisation evaluation will be done at 28 and 36 weeks regarding maternal hemoglobin, serum ferritin, MFI scoring, obstetrical scan for fetal parameters, blood transfusion, development of any complication (preeclampsia, preterm labor, IUGR) and fetal birth weight. Fetal cord hemoglobin and serum ferritin will be checked after delivery. In this way, assessment for primary and secondary outcomes will be done and data set prepared for analysis.

## METHODS

### Participants, Intervention and outcome:

### Study setting:

FAIR trial will be conducted in respective departments of obstetrics of three teaching hospitals of Lahore including Services Institute of Medical Sciences and its Services Hospital, Allama Iqbal Medical College and its Jinnah Hospital, and Fatima Jinnah Medical University and its Sir Ganga Ram Hospital.

### Eligibility Criteria:

Selection criteria is established using the PICO or population, intervention, comparison and outcome framework explained in Table-I.

**Table-I T1:** PICO for study population.

	Population	Intervention	Comparison	Outcome
Inclusion	Singleton pregnancy Haemoglobin 11-13 g/L at booking with ferritin below the threshold (<30) Age >18 years of age at recruitment to the study Able to provide written informed consent Patients willing to enroll in study	NAID patients will be divided into two groups by randomization. One group (usual care/oral group) will be offered the routine care prophylactic dose of oral iron which is 30-45 mg and other group (interventional /IV group) will be offered intravenous therapeutic dose of iron to replenish iron stores which is 1000mg calculated by Ganzoni’s formula. They will continue the prophylactic dose after replenishing iron stores. Adherence to intervention protocols will be monitored by proper documentation and laboratory test	Usual care vs intervention arm will be compared for outcome	Primary: Maternal: Hemoglobin at 36 weeks’ gestation to birth Secondary: Neonatal birthweight or small for gestational age, preterm birth, blood transfusion, preeclampsia, multidimensional fatigue inventory, breast feeding avoidance/initiation, neonatal cord ferritin and haemoglobin

### Participant Timeline:

From booking (<20 weeks) till delivery of the fetus (Fig.1).

**Fig.1 F1:**
[figure not shown]
Flow of participants throughout the FAIR study.

### Sample Size:

Using haemoglobin at 36 weeks as a continuous outcome measure and to confirm or refute a small to medium effect of screening/intervention vs usual care (0.3 SD difference), based on ? = 0.05 and β = 0.1 (90% power), 235 patients in each group (i.e. 470 patients in total) will be required. Considering a 20% loss to follow-up, the sample size is inflated to 300 patients in each group (i.e. 600 patients in total).

### Recruitment:

Patient recruitment service providers in outpatient departments will educate the public about the value of clinical trial participation and will encourage the enrollment. All singleton pregnant women with gestational age <20 weeks coming to outdoor department of respective hospitals will be screened for hemoglobin and serum ferritin. If their hemoglobin ≥11g/dl and serum ferritin concentration <30ug/l they will be enrolled for trial after taking informed consent and randomization will be carried out.

### Methods: Assignment of Interventions

### Allocation:

After recruiting the participants, their data will be entered by investigators sitting in outpatient department in a online computer software program made by technology team that will assign a pin code to every participant which will help in follow up entry of each participant´s data and data analysis by technology team. After randomization, computer software will automatically generate numbers to the participants in an allocation ratio of 1:1 to each group, it will help remove the selection bias. Numbers will be generated from 1-25 randomly by software and after completion of first 25 participants the program will automatically start a new set of 25 numbers. Concealed boxes in sets of 1-25 having IV and oral iron will be made by another team of investigators in respective wards which will be given to the participant having the same computer software generated number.

